**Fig. 2 Fig2:**
[figure not shown]
LTC to ED referral pathway

HCAs’ familiarity with LTC residents put them in an ideal position to identify early changes in a resident’s status, using the Stop-and-Watch tool. Once notified by HCAs of a resident’s change in condition, nurses in LTC will be supported in making decisions using the Change in Condition cards and through early communication with the attending LTC or on-call physician. The goal is to support LTC in early identification and onsite management of changes in health status where appropriate, as well as to improve communication between LTC practitioners. Implementation of INTERACT® tools can result in a significant reduction in hospitalization rates for residents in LTC facilities [24, 25].

The LTC-ED care and referral pathway will serve as a resource for LTC facilities, when making management decisions for LTC residents experiencing an acute change. A call center that serves as a single point of contact for care providers, in order to facilitate care discussions and transfers between facilities (i.e., LTC and ED), will be used to link the LTC physician and nurse to an ED physician. The call centre is called RAAPID (Referral, Access, Advice, Placement, Information & Destination). RAAPID will support a discussion between health care providers regarding the best options for further assessment and care (e.g. ED transfer vs. community paramedicine visit) and help to minimize errors that can occur during transitions in care.

The pathway will also help to further optimize the use of community paramedicine by LTC facilities. The community paramedicine program provides primary and urgent health care to patients in the community, including LTC. The community paramedicine program also has procedures in place to provide facilitated transport to and from diagnostic imaging without an associated ED visit. Studies have shown that the provision of community paramedics within LTC significantly reduces transfers to the ED, improved outcomes, and improved resident and family experiences [12, 26–28].

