### Evaluation plan

The evaluation framework will use a mixed-methods approach, where quantitative and qualitative data collection will occur using a concurrent dominant design. Mixed methods research involves collecting, analyzing, and interpreting quantitative and qualitative data in a single study that investigates the same underlying phenomenon [29]. Mixed methods research is useful for studying complex health issues such as motivations, attitudes, perceptions, beliefs, and values that underlie health behaviours within social, economic, organizational, and political contexts that cannot be captured by either quantitative or qualitative designs alone [30]. The primary outcome will be the change in the rate of transfers to ED from LTC facilities. Specifically, we will compare differences in the rate of transfers per 1000 resident days. This will be used to track the effectiveness of the intervention at the LTC sites (i.e., changes in the rate of transfer before and after the intervention). Data on all LTC-ED transfers are currently collected as part of administrative data by Alberta Health Service Analytics. Over the 30-month study period, our current rate of ED transfers would result in over 8000 LTC-ED transfers from patients within the 38 participating Calgary LTC facilities. After we account for the stepped-wedge design effects and plausible levels of over-dispersion, this will provide 80% power to detect a 15% reduction in the rate of LTC-ED transfers (primary outcome) [15, 31–33].

Secondary outcomes, using data obtained from administrative databases, will include the change in the rate of LTC admissions to hospital per 1000 resident days and the proportion of LTC residents cared for in their LTC facilities through community paramedicine post-pathway implementation. Consenting residents will also evaluate community paramedicine and ED care episodes by completing a modified version of the OPTICS (Older Persons Transition in Care Success; see Additional file 1) Success tool, within 2 days of a community paramedic visit or an emergency department visit that did not result in a hospital admission [31]. The OPTICS tool has been used and validated in previous studies [34, 37].

The appropriateness of the pathway triage decision will be assessed using a random

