sample of up to 50 ED transfers and 50 community paramedicine visits. A standardized data collection form will be used by trained abstractors to extract key elements related to these episodes of care from medical records of consenting patients. A panel of physicians, including emergency physicians, geriatricians and physicians working within LTC, will review these completed abstraction forms to determine appropriateness of the triage decision, using the definitions of unnecessary and avoidable transitions developed in the EXACT (Examining Aged Care Transitions) study. This definition was developed through focus groups and interviews with LTC, EMS (emergency medical services) and ED staff and physicians, and then validated through a larger survey [35]. Additionally, the panel will determine if the treatment plan was concordant with residents’ wishes for treatment and goals of care designation.

Safety reviews of medical records will also be completed for up to 50 consenting patients who are treated by community paramedicine and subsequently transferred to ED within 72 h. A standardized form will be used by trained abstractors to extract key elements related to these episodes of care from medical records. These completed abstraction forms will then be reviewed by the physician panel. Specifically, we will use a previously developed six-point scale to determine the degree to which the ED transfer was the result of suboptimal care provided by community paramedicine [36].

Assessing the economic feasibility of this program is important to informing its scale and spread. A comparative cost-analysis will be undertaken, which includes hospitalizations, ED visits, ambulatory care, urgent care center, and physician and paramedic costs. This resource use is routinely captured by administrative data sets. Patient-level cost data will be provided by administrative data collected by the AHS. We will capture physician costs, hospital costs, as well as the cost of implementing our program.

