In conjunction with AHS analytics we have developed an electronic dashboard specifically designed to support the evaluation of this project. The electronic dashboard was developed by AHS analytics in 2015 on the software Tableau. The dashboard captures monthly data on transfers from facilities. Only selected members of the research team can access the dashboard. Members of the project team (i.e., implementation coach) provide each facility with biannual reports of how the facilities are performing. The dashboard captures data on ED visits from each LTC enrolled in the study per 1000 resident days. RAAPID calls to LTC sites, visits to LTC sites by community paramedicine, and hospital admission rates per 1000 resident days for each facility enrolled in the study. This dashboard will be used as an audit-feedback tool for LTC facilities, as the initiative is scaled up and spread across the province. Additional administrative data captured on the dashboard will include transfer volume, ED arrival mode, primary diagnosis, CTAS score, and EMS events.

The major components of this study have been summarized in Fig. 3.

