### Analysis plan

#### Quantitative analysis

The rate of transfers to ED from LTC facilities will be expressed as the number of ED transfers per 1000 resident days within each three-month cluster period. For our primary outcome, we will use a negative-binomial generalized linear mixed effects model. This model will have random intercepts for sites, an indicator variable for treatment mode in each cluster at each period and time, and fixed effects for time [15]. This model will account for Poisson over-dispersion, as well as correlations among observations within sites [31–33]. As a secondary analysis, we will use an individual-level analysis to determine whether the impact of the intervention depends on available patient-level factors (such as sex) and in a multilevel mixed-effects model with patient-level and site level effects. Generalized linear mixed-effects models will be used to assess a time by intervention effect on other outcomes using the link functions required to meet model assumptions [40].

Descriptive statistics will be used to determine the proportion of LTC residents cared for in their LTC facilities by the community paramedicine program, using the new LTC-ED care and referral pathway. This will be expressed as the number of Mobile Integrated Health (MIH) community paramedic LTC visits per total RAAPID calls from LTC. Descriptive statistics will also be used to present data on the appropriateness and safety of the pathway triage decision. The median and interquartile range will be calculated for the modified OPTICS tool scores for each of the three groups: pre-intervention ED transfer, post-intervention ED transfers, and post-intervention community paramedicine visits. Time series analysis will be used to compare the different groups.

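### A secondary outcome named as a proportion of residents is defined as paramedic visits per RAAPID call, which is not a proportion, does not count residents and can exceed 100%

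*Protocol article*

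**What the plan says.** The Evaluation plan section lists among the secondary outcomes "the proportion of LTC residents cared for in their LTC facilities through community paramedicine post-pathway implementation". The Quantitative analysis section restates it as the "proportion of LTC residents cared for in their LTC facilities by the community paramedicine program, using the new LTC-ED care and referral pathway", assigns it to descriptive statistics, and gives the formula: "This will be expressed as the number of Mobile Integrated Health (MIH) community paramedic LTC visits per total RAAPID calls from LTC".

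Three other statements bear on how that formula behaves.

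- The Intervention section describes a standing service: "The community paramedicine program provides primary and urgent health care to patients in the community, including LTC". It adds: "The pathway will also help to further optimize the use of community paramedicine by LTC facilities".
- The Evaluation plan lists the dashboard contents for each facility as separate items, among them "RAAPID calls to LTC sites, visits to LTC sites by community paramedicine, and hospital admission rates per 1000 resident days". It describes no link between a given call and a given visit.
- The Evaluation plan sets up a safety review of a sample of consenting patients "treated by community paramedicine and subsequently transferred to ED within 72 h".

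**The concern.** The outcome's name and its formula describe different quantities. The name promises a share of residents, between 0 and 100%, whose acute episode was handled on site. The formula divides a count of visits by a count of telephone calls. Nothing in the text makes the visits a subset of the calls, limits a resident or an episode to one visit, or removes visits that ended in the ED.

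This goes beyond detail that an article may leave to a fuller document. The article states the rule, and following it gives a number that does not measure the outcome as named. A reader told that some percentage of residents were cared for in their facility would be misinformed. If visits from outside RAAPID enter the numerator, a change in the ratio could also be misread as a success of the pathway when it reflects fewer calls.

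**Working it through.** The documents give no value for this outcome, so there is no figure to reproduce. The check compares units and then works through the algebra of the stated ratio.

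**Units.** As named: residents over residents. As defined: visits over calls. The two agree only if every counted visit comes from a RAAPID call, each call yields at most one visit, each resident has one call, and every visited resident stays in the facility. None of these conditions is stated.

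**Algebra.** The symbols are as follows; none has a value in the documents, so all values below are assumptions.

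- C: RAAPID calls from LTC
- q: share of calls sent to paramedicine
- m: visits per such call
- D: paramedic visits to LTC that did not start with a RAAPID call

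The planned measure is R = (q·m·C + D) / C = q·m + D/C.

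**Can it exceed 1?** There are two routes.

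1. Repeat visits alone (D = 0). With q = 0.5 and m = 2.5, R = 0.5 × 2.5 = 1.25.
2. Visits outside RAAPID. With q = 0.5, m = 1 and D = 20, R = 0.5 + 20/C. This gives 0.70 at C = 100, 0.83 at C = 60, 1.00 at C = 40 and 1.50 at C = 20.

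**How does it respond to uptake?** Take 100 acute episodes with q = 0.5 and m = 1. Let a proportion u of episodes generate a RAAPID call, so C = 100u. Let a proportion d of the remaining episodes get a paramedic visit directly, so D = d(100 − C). The share of all episodes seen by a paramedic is (0.5C + D)/100.

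| u | R, d = 0 | Share seen | R, d = 0.1 | Share seen | R, d = 0.3 | Share seen |
|---|---|---|---|---|---|---|
| 0.9 | 0.50 | 0.45 | 0.51 | 0.46 | 0.53 | 0.48 |
| 0.6 | 0.50 | 0.30 | 0.57 | 0.34 | 0.70 | 0.42 |
| 0.3 | 0.50 | 0.15 | 0.73 | 0.22 | 1.20 | 0.36 |
| 0.1 | 0.50 | 0.05 | 1.40 | 0.14 | 3.20 | 0.32 |

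One cell in full, for u = 0.3 and d = 0.3: C = 30, D = 0.3 × 70 = 21, R = (15 + 21)/30 = 1.20, share seen = (15 + 21)/100 = 0.36.

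When direct visits are counted (d > 0), R rises as uptake falls, while the share of episodes seen by a paramedic falls. When they are not counted (d = 0), R does not move with uptake. It is then not inverted, but it says nothing about how far the pathway was used.

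**Visits followed by ED transfer.** If a fraction f of calls with a visit end in ED transfer within 72 h, the share of calls resolved on site is q(1 − f) at m = 1 and D = 0, whereas the formula gives q. The documents give no f, so the overstatement cannot be sized.

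**The case against.** The strongest defence is that the sentence before the formula limits the outcome to care delivered through the new pathway, and the formula refers back to that sentence. On that reading only pathway visits count, so D = 0 and the ratio does not rise when uptake falls. The Intervention section does not say how paramedic visits are requested, and the pathway figure is not available here, so visits that bypass RAAPID after implementation are plausible but undocumented. This stands as a limit on the uptake argument. It does not rescue the definition: visits are still not residents, repeat visits can still take the ratio above 1, and visits followed by ED transfer still count.

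It can also be said that keeping a utilisation measure apart from the physician panel's safety review is a legitimate choice. That is so, but the outcome is named as care received in the facility, and the formula does not honour the name.

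Several stronger readings are tempting and should not be drawn.

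- A reader might infer that this ratio is the only quantitative evidence on whether care moves out of the ED. It is not: ED transfers per 1000 resident days are the primary outcome, hospital admissions are another secondary outcome, and ED and paramedic costs are compared.
- A reader might infer that a facility ignoring RAAPID will score highest. That needs visits outside RAAPID to be counted, no ranking of facilities on this ratio is planned, and at zero calls the ratio is undefined.
- A reader might infer that the ratio will exceed 100% in this trial. The documents contain no counts that would show it.
- The dashboard wording, "RAAPID calls to LTC sites, visits to LTC sites by community paramedicine", reverses the direction of the calls given in the formula. The Intervention section makes clear that RAAPID connects LTC clinicians to an ED physician, so this is a wording slip to tidy.
- Restricting the measure to the period after implementation fits a descriptive measure of the new pathway and is not an error.

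**Conclusion.** The point holds for the definition. The formula does not estimate the proportion that the outcome names, is not bounded by 100%, and counts as on-site care some episodes that ended in the ED. This follows from the text with no assumed values.

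The claim that the ratio can rise as RAAPID uptake falls is conditional. It requires that visits not arising from a RAAPID call are counted, which the description of a standing paramedicine service makes plausible but the article does not state. The figures in the working illustrate the behaviour under assumed q, m, D and d; they are not predictions for these 38 facilities.

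The consequence is limited. The outcome is secondary and descriptive, carries no test or power claim, and does not enter the primary negative-binomial analysis. It should be fixed before results are reported, but it does not threaten the trial's main conclusion.

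**What to change.** 1. Redefine the measure. Numerator: RAAPID calls from LTC that led to at least one community paramedic visit with no ED transfer within 72 h, each call counted once. Denominator: all RAAPID calls from LTC. This is bounded by 100%, and the window matches the one already used for the safety review. Name it as a proportion of calls, not of residents.
2. If calls and visits cannot be linked, keep the planned figure but label it a visits-per-call ratio, and say whether visits that did not start with a RAAPID call are included.
3. Report paramedic visits and RAAPID calls per 1000 resident days as two separate rates, so that low uptake is visible. Compare the visit rate between control and intervention periods, using the facility-level dashboard data and the mixed-model framework that the plan already specifies for other outcomes.
4. Use one wording for the direction of the calls throughout.

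The cost is a change of outcome wording, one further rate analysis, and, for item 1, linkage of call, visit and ED records. The article does not describe that linkage, so the sponsor should confirm that it is feasible. Items 2 to 4 do not depend on it.

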**Fig. 1 Fig1:**
[figure not shown]
Implementation of a stepped wedge design

By the end of the study, all 38 participating LTC facilities will have received the intervention. However, the order in which facilities receive the intervention will be determined at random [14]. A stepped-wedge design is an ideal design to evaluate an intervention on a population level, where there are implementation resource constraints. This design is also useful where there are ethical or community concerns that all participating sites should eventually get the intervention. As a crossover design, it also controls for confounding and site-level differences because each site is observed before and after the intervention. Therefore, changes within the wider health system over time can be observed, given data is available from multiple pre-intervention and intervention sites at various points in time [15].

The intervention will be implemented at four to five LTC facilities each quarter (every 3 months), with all facilities having implemented the intervention in 30 months. The pre-implementation phase will take place over 1 month. During the pre-implementation phase the researchers contact the participating sites, meet with site leaders and staff, conduct a barriers to implementation assessment, provide the overarching rationale for the implementation program and outline the plan for implementation (i.e., setting an implementation workshop and determining what additional resources are required). Baseline data with the OPTIC tool and chart abstractions will be done prior to the intervention, with implementation occurring over the subsequent 2 months. The intervention will then become an expected standard care practice at the facility, and thus this will be considered the post-implementation phase.

The order of implementation will be randomized using random number generation to reduce bias, where the unit of randomization is the LTC facility. LTC facilities with the same owner-operator will be randomized to the same implementation period, given that these facilities often share staff. Until the pathway is implemented at a LTC facility, facilities will act as controls for the purposes of analysis.

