### Study participants

Administrative data related to LTC resident visits by a community paramedic(s) and/or emergency department visits will be included for the 38 participating facilities. Consenting LTC residents and family members will complete the OPTICS tool with between five to 12 participants being recruited per facility. Residents will typically be long-stay residents. Fifteen to thirty eligible and consenting LTC residents and family members will participate in interviews. Thirty-six to seventy-two health care providers working within the participating LTC facilities, community paramedicine, and emergency departments will be asked to participate in focus groups.

Inclusion criteria for recruitment of residents or their family members include
LTC Resident has been seen by a community paramedic(s) OR has returned directly from the emergency department within the past 2 days (i.e., 72 hours) and they were not admitted to the hospital.The residents are not acutely confused.Must have a RAI CPS (Cognitive Performance Scale) score of 2 or less completed within the past 6 months.Do not have an enacted personal care directive (i.e., they are still able to make their own care decision)LTC Residents > 65 yearsIf the LTC resident does not meet these criteria but there is a family member who is regularly visiting the LTC resident, the family member can be approached while visiting the LTC facility for permission to be contacted.

Focus groups will be conducted with physicians, nurses, community paramedics and health care aides, who are direct care staff in LTC facilities. Inclusion criteria for LTC and ED health practitioners.
Physicians, staff (i.e., nurses and health care aides), or community paramedics associated with the LTC or ED must be familiar with or must have utilized the RAAPID pathway during the duration of the study.Nurses and health care aides must have used the INTERACT® and STOP and WATCH tools during the study to aid in their decision making.

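### OPTICS scores are compared across groups set by the pathway's own triage, with no paramedicine baseline and a time series method that sparse data cannot support

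*Protocol article*

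**What the plan says.** The Evaluation plan section has consenting residents score paramedicine and ED episodes with the modified OPTICS tool, "within 2 days of a community paramedic visit or an emergency department visit that did not result in a hospital admission". Study participants puts the sample at "between five to 12 participants being recruited per facility".

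The Quantitative analysis section then fixes the analysis. On the summary: "The median and interquartile range will be calculated for the modified OPTICS tool scores for each of the three groups". On the groups and their comparison: "pre-intervention ED transfer, post-intervention ED transfers, and post-intervention community paramedicine visits. Time series analysis will be used to compare the different groups". No time unit, model or covariates are given for it.

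Three other statements bear on this:

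- The Intervention section describes paramedicine as an existing service to LTC whose use the pathway will optimise further. It also says the call centre supports the choice between ED transfer and a paramedic visit.
- The Discussion names fewer transfers and more paramedicine as the expected effect.
- The Study design section says baseline OPTICS data are collected before the intervention, and the inclusion criteria admit residents seen by a paramedic without limiting this to the period after it.

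On timing, the inclusion criteria for residents and families give the window as "within the past 2 days (i.e., 72 hours".

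**The concern.** The groups are formed by period and by place of care, and place of care is what the pathway changes. After implementation, the ED group has lost the residents who were diverted and the paramedicine group has gained them. If diverted episodes differ in severity from those still sent to ED, scores can differ between groups without any resident being cared for better or worse. The listed groups include no pre-intervention paramedicine episodes against which the third group could be judged.

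A time series method needs a reasonably dense series of observations. A few respondents per facility do not supply one, and nothing is said for OPTICS about correlation within a facility. At stake is the protocol's quantitative measure of resident experience of ED and paramedicine care. The primary outcome is not affected.

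The window is a separate, purely textual matter: two days is 48 hours, not 72.

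**Working it through.** The protocol states no power, effect size or standard deviation for OPTICS, so there is no figure of its own to reproduce.

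**1. How much data there is.** Inputs: 38 facilities (Study design: "By the end of the study, all 38 participating LTC facilities will have received the intervention"), 5 to 12 respondents each (Study participants), 30 months in three-month periods, i.e. 10 quarters.

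- Total: 38 × 5 = 190 to 38 × 12 = 456.
- Per facility-quarter, all groups together: 5/10 = 0.5 to 12/10 = 1.2.
- If split equally over three groups (an assumption): 190/3 ≈ 63 to 456/3 = 152 per group; 5/3 ≈ 1.7 to 12/3 = 4 per group per facility; about 6 to 15 per group per quarter over all sites.

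There is no usable facility-level series. A pooled series would be thin, and the facilities behind it would change each quarter as sites cross over.

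**2. Sorting with no true effect, in points.** The 15% reduction in transfers is the protocol's design figure (Evaluation plan). Assumptions: milder episodes score 80 and sicker ones 60; 40% of pre-intervention ED episodes are milder; every diverted episode is milder and goes to paramedicine; nobody's score changes.

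- ED before: 0.40 × 80 + 0.60 × 60 = 68.
- Milder share of ED after: (0.40 − 0.15)/0.85 = 0.294. ED after: 60 + 20 × 0.294 = 65.9.
- Diverted paramedicine episodes: 80.
- ED after minus before: 65.9 − 68 = −2.1. Paramedicine minus ED after: 80 − 65.9 = +14.1. Paramedicine minus ED before: 80 − 68 = +12.
- All scored episodes after: 0.85 × 65.9 + 0.15 × 80 = 68, unchanged.

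**3. The same in SD units, over a range.** Let p be the milder share before and D the score gap in SDs. The milder share after is q = (p − 0.15)/0.85. The spurious differences are −D(p − q) for ED after versus before, D(1 − p) for paramedicine versus ED before, and D(1 − q) for paramedicine versus ED after. Taking p from 0.3 to 0.7 and D from 0.3 to 0.8:

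| Contrast | Range (SD) | p = 0.5, D = 0.5 | Chance of a false significant result in that direction, p = 0.5, D = 0.5, 63 to 152 per group |
|---|---|---|---|
| ED after − ED before | −0.02 to −0.10 | −0.04 | 4% to 6% |
| Paramedicine − ED before | +0.09 to +0.56 | +0.25 | 29% to 59% |
| Paramedicine − ED after | +0.11 to +0.66 | +0.29 | 38% to 73% |

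The test is two-sided at 5% and ignores clustering, so the nominal chance in one direction is 2.5%. Over the whole range, the first contrast reaches about 3% to 14%.

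**4. Why the baseline matters.** Add to step 2, per 100 ED episodes before, m paramedicine episodes that score 80 and occur in both periods. All episodes after then average (6800 + 80m)/(100 + m). Compared with ED alone before (68), the spurious difference is 12m/(100 + m), which is positive for any m above 0. With the m baseline episodes included it is zero.

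**The case against.** Describing experience by place of care is a legitimate aim, and a median and interquartile range per group is a suitable display for it. An article leaves model detail to a fuller plan, and the Quantitative analysis section does promise generalized linear mixed models for other outcomes. The scores and severity mix used above are invented. The pooled contrast is itself selected: it omits ED visits that end in admission and residents managed onsite with neither service, and the pathway may shift both.

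Much of this stands, and it limits the point. A reader might infer that group differences will be reported as a change in care quality; the article never says so, and the text supports only that they could be mistaken for one. A reader might infer that clustering is ignored; the time series model is unspecified, so site terms are neither included nor excluded. A reader might infer that no pre/post comparison of all episodes is possible; eligibility is not restricted by period, and what is fixed is the list of groups.

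It does not remove the point. The mixed-model sentence does not name OPTICS, which is given its own method. If it is meant to cover OPTICS, the section names two methods for one outcome. Nor can a later analysis plan recover baseline paramedicine respondents who were not recruited before a site crossed over.

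**Conclusion.** The point holds for what the article fixes: comparison groups that depend on the pathway's triage, no listed paramedicine baseline, and a method that does not fit 0.5 to 1.2 responses per facility-quarter.

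The exposure lies in the two contrasts with paramedicine: about +12 and +14 points in the example, or +0.09 to +0.66 SD over the range tried. A stronger reading, that ED care before versus after would be badly distorted, is not supported: at the protocol's own 15% that shift is about −2 points, and at most about 0.1 SD in size.

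These sizes rest on assumed scores, an assumed severity mix and all diverted episodes being milder. The direction would reverse if milder episodes scored lower. The protocol gives no data to settle either.

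The window contradiction stands on the text alone and lends no weight to the rest. This is a worthwhile correction to a secondary outcome and leaves the primary analysis untouched.

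**What to change.** - Replace time series analysis for OPTICS with a linear or ordinal mixed model with random effects for site and effects for calendar period.
- Make the main contrast all eligible scored episodes (ED without admission plus paramedicine) in control versus intervention periods. Recruit pre-intervention paramedicine episodes within the planned 5 to 12 respondents per facility. Adding them only as a fourth separate group would not be enough, because the paramedicine mix also shifts with diversion.
- Let the pooled sample reflect the actual mix of ED and paramedicine episodes, by sampling or by weighting; the cancellation in step 2 depends on it.
- Report the place-of-care groups descriptively. State that admitted and onsite-managed residents are not covered, so some selection remains.
- Reconcile the OPTICS window in the Evaluation plan and Study participants sections to one figure.

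The cost is more than wording. Four groups from the same respondents leave about 5/4 ≈ 1.3 to 12/4 = 3 per group per facility. Baseline recruitment of paramedicine episodes is extra work, and its yield is unknown. The total sample need not grow.
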